# 10.6-μm infrared laser as adjuvant therapy for diabetic peripheral neuropathy: study protocol for a double-blind, randomized controlled trial

**DOI:** 10.1186/s13063-021-05901-6

**Published:** 2022-01-18

**Keywords:** Diabetic peripheral neuropathy, Traditional Chinese medicine, Laser moxibustion, Nerve conduction velocity

## Abstract

**Background:**

Diabetic peripheral neuropathy (DPN) is the most common chronic neurological complication. It is the main cause of disability in diabetes mellitus (DM) patients and seriously affects the quality of life of patients. Pharmacological treatments always associate with limited efficacy and adverse effects. Moxibustion has been recommended to treat DPN as an adjuvant therapy to conventional medical treatment to accelerate alleviation of the symptoms of DPN. 10.6-μm laser moxibustion (LM), whose wavelength is close to the peak of infrared radiation spectrum of the traditional moxibustion as well as human acupoints, produces the thermal effect similar with moxibustion but with no smoke or smell. The purpose of this sham controlled clinical trial is to determine the effect and safety of 10.6-μm LM as adjuvant therapy in patients with DPN.

**Methods:**

This is a protocol for a randomized, double-blind, sham-controlled trial. One hundred fourteen patients meeting the inclusion and exclusion criteria will be recruited and randomly assigned to the LM group or the sham LM group with a 1:1 allocation ratio. Patients in both groups will receive a basic integrated treatment of Chinese and Western medicine and a total of 12 sessions of true or sham LM treatments over 4 weeks with 3 sessions a week. The primary outcome is nerve conduction velocity (NCV), and the secondary outcomes include Michigan Neuropathy Screening Instrument (MNSI) scores, Diabetes-Specific Quality of Life (DSQL) scores, blood rheology parameters, and assessments of safety and blinding. Outcome measures will be collected at baseline, 2 weeks after treatment, the end of LM treatments (4 weeks), and 4, 8 weeks after the end of LM treatment (8, 12weeks).

**Discussion:**

This study will be conducted to compare the efficacy of LM versus sham LM combined with medical treatment. 10.6-μm LM may alleviate symptoms, improve quality of life, and reduce the dosage of drugs as well as avoid causing serious side effects.

**Trial registration:**

Chinese Clinical Trial Registry ChiCTR2000029329. Registered on 25 January 2020.

## Background

Diabetes mellitus (DM) is a chronic systemic metabolic disease caused by a variety of reasons. According to an estimate by the International Diabetes Federation (IDF) in 2015, there were 415 million adults worldwide suffering from DM, about 8.8% of the adult population, and the figure was expected to exceed 600 million by 2040 [1]. In addition to the harm of diabetes itself, the chronic complications caused by diabetes are also the primary reasons affecting patients’ life quality and life expectancy. Diabetic peripheral neuropathy (DPN) is the most common chronic neurological complication of DM; the prevalence of DPN among DM patients is about 30~50% [2–5]. DPN develops as a consequence of long-standing hyperglycemia [6]. The mechanisms of DPN mainly involves activation of polyol pathway, advanced glycation end products (AGEs), dyslipidemia, oxidative stress, and lack of neurotrophic factors [7–9]. The main clinical manifestations of DPN are numbness or pain in both extremities, as well as paresthesia such as formication or burning sensation. DPN plays a key role in the development of diabetic foot complications [6]. About 15–20% of diabetic foot ulcers require amputation [10, 11]. More than 60% of the patients may suffer from sleep disorders caused by diabetic peripheral neuropathy pain (DPNP), which even may lead to anxiety, depression, and other mental disorders [12]. In addition, DPN is associated with skeletal muscle deficits such as neurogenic muscle atrophy and myasthenia [13]. DPN is the main cause of disability in DM patients and seriously affect the quality of life of patients. Additionally, DPN is associated with a huge human and economic burden on both the patients and the health care system [14, 15]. In addition to drugs that control glucose (such as insulin), α-lipoic acid, mecobalamin, nimodipine, angiotensin-converting enzyme (ACE) inhibitors, epalrestat, and some medicine for pain management such as anti-convulsants, and tricyclic antidepressant drugs are commonly used to treat DPN [5]. But theses medicines always associate with limited efficacy and adverse effects as well as higher costs [16–19].

Non-pharmacological treatments have also been proposed to treat DPN combined with pharmacological treatments to accelerate regeneration of the injured nerve. Moxibustion, a traditional Chinese medicine method with moxa burning over the acupuncture points, has been recommended to treat DPN [20]. Some clinical trials showed that moxibustion had positive effects on nerve conduction velocity (NCV) and clinic symptoms caused by DPN [21–23]. However, the burning moxa produces an annoying smoke and smell, which is irritating and might be harmful to both the patients and practitioners and might limit the use of moxibustion in the clinic [24, 25]. Like moxibustion, low level laser therapy (LLLT) is one of the common non-pharmacological treatments for DPN [26]. LLLT may produce biological stimulation to the nervous system [27]. CO_2_ laser is a far-infrared laser with the wavelength of 10.6 μm, which is close to the peak of infrared radiation spectrum of the traditional moxibustion and human acupoints [28, 29]. In addition, CO_2_ laser can be absorbed within 0.2 mm of the epidermis and produce a fast, marked, and lasting thermal effect on the skin surface like traditional moxibustion [30, 31]. We have developed a laser moxibustion (LM) device of 10.6 μm wavelength, which has the thermal nature of moxibustion without smoke and smell. Our previous studies showed that 10.6-μm LM may be effective in alleviating the symptoms of knee OA [32–34]. We also found that the 10.6-μm LM and the traditional moxibustion may result in similar effects in treating knee OA [35]. Besides, animal experimental results showed 10.6-μm LM can alleviate the neuropathic pain induced by oxaliplatin and increase the blood perfusion of the skin. However, there is no high-quality clinical research to evaluate the effects and safety of 10.6-μm LM in treating DPN.

The purpose of this placebo controlled clinical trial is to determine the effect of 10.6-μm LM on motor and sensory nerve conduction velocity (NCV), symptoms (clinical scores) and safety in patients with DPN.

## Methods/design

### Trail design

This is a randomized, double-blind, placebo-controlled trial to compare the effectiveness and safety of 10.6-μm LM with sham laser control in treating DPN. This trial will be conducted in the endocrine department of Shanghai Municipal Hospital of Traditional Chinese Medicine.

This trial has been approved by the Institutional Review Board (IRB) of Shanghai Municipal Hospital of Traditional Chinese Medicine (Approved No.: 2019SHL-KY-37). Trial registration: Chinese Clinical Trial Registry, ChiCTR2000029329. Registered 25 January 2019—retrospectively registered, http://www.chictr.org.cn/edit.aspx?pid=48490&htm=4

Eligible patients will be randomly assigned into 2 groups (the LM group or the sham LM group) with a 1:1 allocation ratio. The patients in both groups will receive a total of 12 sessions of LM treatments over 4 weeks with 3 sessions a week, and the treatment will be given once every other day and lasts 15 min for each acupoint for each session. The outcomes will be measured at baseline, midterm (2 weeks after treatment), the end of LM treatment (4 weeks after treatment), and follow-up (4 、8 weeks after the end of LM treatment) (Fig. 1).

**Fig. 1 Fig1:**
[figure not shown]
Study flow chart

### Sample size

According to the studies [36, 37], we assume that the peroneal motor nerve conduction (MNCV) velocity in the LM group increases by 38% after treatment and that in the sham LM group by 16% after treatment. Fifty-one patients per group will be required with an alpha of 0.05 and a power of 0.8. Considering possible drop-out (i.e., 10% drop-out) during the trial, we will recruit 57 patients for each group.

### Study population

#### Inclusion criteria

Diagnosed with DPN [38] in both lower extremitiesAged 18–75 years old, no limit on genderDelayed nerve conduction velocity in lower extremitiesStable blood glucose levels (Stable levels of HbA1c during the last 6 months)Understanding and signing the informed consent

#### Exclusion criteria

Neuropathy or chronic pain caused by conditions other than diabetesDPN most prevalent in the upper limbsPresence of serious medical conditions including kidney diseases, heart diseases, pulmonary diseases, liver diseases or contagious diseases, or malignant tumors and serious psychopathyPrevious history of knee/hip replacement surgery or bone fracture of the lower extremities during the last 3 months and other conditions that would confound assessment of neuropathyUlceration and other diseases at the lower extremitiesAcupuncture or moxibustion treatment received in the previous 3 monthsLLLT received in the previous 3 monthsUsing other external therapy simultaneouslyOpiate, analgesic, illicit drug, or alcohol abuseUnwillingness to be randomly assigned into either a treatment or a placebo groupUnable to fill measurement questionnairesRecruited in other clinical trial simultaneouslyPregnant or breast-feeding women

#### Withdrawal criteria

Serious adverse events during the treatmentWithdrawal demanded by the participantUse the treatment method prohibited by the program or change the treatment method by the participant

#### Principles of management of withdrawal

Record the last treatment time and complete the evaluation items that can be completedIntention analysis was performed on all cases after the end of the trial

### Randomization and blinding

The researcher will screen the patients strictly according to the inclusion and exclusion criteria. Eligible patients will be randomized in a ratio of 1: 1 into two groups: LM group or the sham LM group. The random assignment sequence will be generated by the researcher A who does not participate in other processes of the trial using SPSS software.

LM devices (either active or sham devices) will use different numbers as codes. The random assignment sequence will be placed in a serially numbered, opaque, sealed envelope with a copy paper inside by researcher A. Researcher B who will enroll participants will open the envelope in sequence after writing the basic information of the patient on the envelope surface before opening the envelope and informs the device operators of the device code assigned to the patient. Active or sham devices will be operated by trained operators separately.

The sham LM device is identical with the LM device in appearance, and operational procedure. The patients will be informed as follows in consent before randomization: “You will receive either 10.6 μm LM or non-10.6 μm LM treatment. You might feel any sensations (e.g., heat, cold, no feeling, or else) from this device. However, neither of the two methods can guarantee the curative effect…I have been told that I may be assigned randomly in 10.6 μm LM group or non-10.6 μm LM group [39].” Besides, the two groups of patients will be treated in separate rooms or treatment time to avoid communication among patients. Therefore, patients, researcher screening patients, device operators, outcome assessors, data entry researchers, and statistical personnel will be blinded to the treatment allocation.

### Consent

Before randomization, the patients will be informed the whole procedure of the trail and possible benefits or side effects by the researcher B. And then, written consent will be obtained from each participant.

### Intervention

#### Laser moxibustion device and sham device

The LM devices (SX10-C1) were manufactured by Shanghai Wonderful Opto-Electrics Tech. Co., Ltd. (Shanghai, China) and licensed by Shanghai Municipal Food and Drug Administration, China (20162210783) (Fig. 2). The wavelength of the infrared laser is 10.6 μm; the output power is set between 140 and 160 mW. The sham LM device is identical with the LM device in appearance, weight, sound, and operational procedure but without laser output. However, in both active and sham devices, a red light-emitting diode with an output of 3 mW is used as visible indicator light on the skin to confirm accuracy of irradiation on the targeting acupoint.

**Fig. 2 Fig2:**
[figure not shown]
The LM devices (SX10-C1)

#### Treatment protocol

Patients in both groups will receive LM or sham LM therapy and a basic concurrent therapy.

##### Laser moxibustion therapy

The patients will be told to lie down on their backs with the subknee area exposed entirely. The irradiation tips of the two LM devices will be aimed to the surface of the acupuncture points. The acupuncture points that are irradiated are the bilateral ST36 (*Zú Sān Lǐ*), GB34 (*Yáng Líng Quán*), SP6 (*Sān Yīn Jiāo*), and KI3 (*Tài Xī*) at the lower limbs. The location of all acupoints refers to the textbook *Acupuncture and Moxibustion* [40] (Table 1). The distance between the tips and the skin is about 2 cm, and the light spot is 2 cm in diameter on the skin. Each acupuncture point will receive 15 min irradiation of the LM device or sham LM device for one treatment. Energy density ranges from 40.13 to 45.86 J/cm^2^ for one session of treatments. The patients in both groups will receive a total of 12 sessions of treatments over 4 weeks with 3 sessions a week, and the treatment will be given once every other day. If the participants cannot participate a treatment session on schedule, he/she will be required to make it up within that week. The sham device is operated in the same way but there is no laser output.

**Table 1 Tab1:** Acupuncture point selection

point	location
ST36(*Zú Sān Lǐ*)	On the anterior aspect of the leg, on the line connecting ST35 (*dú bí*) with ST41 (*jiĕ xī*), 3 cun inferior to ST35
GB34 (*Yáng Líng Quán*)	On the fibular aspect of the leg in the depression anterior and distal to the head of the fibula
SP6 (*Sān Yīn Jiāo*)	On the tibial aspect of the leg, posterior to the medial border of the tibia, 3 cun superior to the prominence of the medial malleolus
KI3 (*Tài Xī*)	On the posteromedial aspect of the ankle, in the depression between the prominence of the medial malleolus and the calcaneal tendon

##### Concurrent therapy

Patients in both groups will receive basic treatment such as blood sugar control according to patients’ condition. For the treatment of DPN, detailed recommended treatment plan is listed in Table 2. Any changes in the use of medications (including date of administration, types, and dosage) will be recorded in detail.

**Table 2 Tab2:** Plan of the basic integrated treatment of Chinese and Western medicine

Medicine	Route of administration	Timing of administration
α-Lipoic acid 60 mg	Intravenous drip	Once a day from week 1 to week 2
Methycobal	Intravenous injection (1000 μg)	Once a day from week 1 to week 2
	Oral administration (500 μg)	Three times a day from week 3 to week 4
Epalrestat 50 mg	Oral administration	Three times a day from week 1 to week4

### Outcome measures

#### Primary outcome

##### Nerve conduction velocity (NCV)

NCV will be performed on both lower extremities at baseline and the week 4 (the end of treatment). Peroneal motor nerve conduction velocity (MNCV), sural sensory nerve conduction velocity (SNCV), and tibial motor nerve conduction velocity (MNCV) will be measured.

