### Statistical analysis

The statistical analysis will be performed using SPSS version 21.0 software. All continuous data that follow the normal distribution will be expressed as mean ± standard deviation (); data that do not conform to the normal distribution will be expressed as median (Q1, Q3). And categorical data will be expressed in terms of the number of cases. If the general numerical data follow normal distribution, then the independent sample *t* test will be used to analyze the differences between the two groups at different points in time. If the values do not follow normal distribution, then the Wilcoxon Mann-Whiney *U* rank sum test will be used. Chi-square test and Mann-Whitney *U* test will be used to analyze the categorical data. Differences are considered statistically significant at a *P* value less than 0.05.

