In our study, we will use the nerve conduction study (NCS) as the primary outcome. NCS is also one of the objective measures in the diagnosis of DPN with high sensitivity and accuracy [44]. Besides, we will use the symptoms and examination outcome measurement (MNSI) to evaluate the severity of the symptom. The subjective outcome (DSQL) will be used to assess the influence of the treatment on patients’ quality of life. The blood rheology parameters will be used to assess the effect of 10.6-μm LM on improving blood rheology and decreasing blood viscosity in DPN patients.

There are two limitations of our study. Firstly, we focus more on the clinical effect of LLLT on DPN, not much attention has been paid to the possible mechanism of LLLT on DPN. Secondly, due to the limitations of the device, one treatment will last for 30 min, but each acupoint will be irradiated for 15 min.

A study showed that the increasing of NCV in the mecobalamin combined moxibustion group was higher than that in the mecobalamin alone group at the same endpoints [36]. Thus, we anticipate the 10.6-μm LM which shared similar infrared effect with the traditional moxibustion may result in similar curative effect and reduce the dosage of drugs as well as avoiding the serious side effects caused by western medicine. We expect this double-blind, sham-controlled trial will provide rigorous evidence for the effect and safety of 10.6-μm LM as adjuvant therapy in treating DPN.

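### Three nerve velocities share the primary outcome and none is named as decisive, while the alpha and power were set for peroneal MNCV alone

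*Protocol article*

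**What the plan says.** The Abstract identifies the primary outcome only by its general name: "The primary outcome is nerve conduction velocity (NCV". The Discussion is wider still: "we will use the nerve conduction study (NCS) as the primary outcome".

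The detail is in the primary outcome section, which lists three velocities: "Peroneal motor nerve conduction velocity (MNCV), sural sensory nerve conduction velocity (SNCV), and tibial motor nerve conduction velocity (MNCV) will be measured". On limbs and timing it says: "NCV will be performed on both lower extremities at baseline and the week 4 (the end of treatment".

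The Sample size section uses one of the three: "we assume that the peroneal motor nerve conduction (MNCV) velocity in the LM group increases by 38% after treatment". For the sham arm it takes a rise of 16% in the same variable. It concludes: "Fifty-one patients per group will be required with an alpha of 0.05 and a power of 0.8". It does not call peroneal MNCV the primary endpoint.

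The Statistical analysis section gives a t test or a rank-sum test for continuous data and one criterion for everything ("Differences are considered statistically significant" when P is below 0.05). It does not rank the three velocities, adjust for them, or say whether one or all must succeed.

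**The concern.** A confirmatory trial needs to fix in advance which comparison decides it. Here the outcome section offers three candidates and the sample size section uses one, and no sentence joins the two. As written, a significant difference in the peroneal, sural or tibial nerve could each be presented as a positive primary result. The 5% error rate would then not apply to the trial's main claim, and the 80% power would describe only one of three routes to it.

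This is more than a detail left to an analysis plan. A plan commonly holds the adjustment method, but the choice of primary variable belongs in the protocol, and two sections of this one do not match on it.

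**Working it through.** **Inputs from the protocol article**
- Velocities under the primary outcome: 3 (primary outcome section).
- Post-baseline time points for NCV: 1, week 4 (same section and Table 3). Repeated visits therefore add no multiplicity.
- Threshold: P < 0.05 (Statistical analysis). I take it as two-sided; the article does not say.
- Planning variable: peroneal MNCV, +38% against +16%, alpha 0.05, power 0.8, 51 per group, 10% drop-out, 57 recruited per group (Sample size).

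**Assumption:** the correlations between nerves. The article gives none, so a range is shown.

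**1. The plan's own sample size.** The drop-out step reproduces: 51 / 0.9 = 56.7, rounded up to 57. The 51 cannot be rebuilt as a comparison of means, because no standard deviation is given. Taken at face value as a two-sided comparison of means, 51 per group implies a standardized difference of

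d = (1.960 + 0.842) × √(2/51) = 0.555,

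that is, a standard deviation of 22 / 0.555 ≈ 39.7 percentage points. I use d = 0.555 below only to show what happens to power. Whether 51 is well founded is a separate matter.

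**2. Chance of at least one false positive among three tests.** For independent tests this is 1 − 0.95³ = 14.3% two-sided, and 1 − 0.975³ = 7.3% in the direction favouring LM. For correlated tests I simulated equicorrelated normal statistics (at least 1,000,000 draws) with cut-off 1.96:

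| Correlation between nerves (assumed) | Two-sided | Favouring LM |
|---|---|---|
| 0 | 14.3% | 7.3% |
| 0.3 | 13.6% | 6.8% |
| 0.5 | about 12.5% | 6.3% |
| 0.7 | 10.9% | 5.5% |
| 0.9 | 8.4% | 4.2% |
| One test, for reference | 5.0% | 2.5% |

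**3. If all three stay as alternative primaries.** The Bonferroni level is 0.05 / 3 = 0.0167, with critical value 2.394. With d = 0.555 and 51 per group, the expected test statistic is 0.555 × √(51/2) = 2.80. Power for one nerve is Φ(2.80 − 2.394) = 66%. Restoring 80% needs 2 × (2.394 + 0.842)² / 0.555² = 68.03, so 69 per group, or 69 / 0.9 = 76.7, so 77 with drop-out. Holm's procedure starts at the same 0.0167 and relaxes only after another nerve has succeeded. For a single nerve its power is therefore at least 66%, and close to that when the other two show nothing.

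**4. If all three had to succeed.** The error rate would not be inflated. Power would fall below 80%: with 80% for each nerve and independence it would be 0.8³ = 51%, and higher with positive correlation. The article states no such rule.

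**5. If peroneal MNCV is the single primary.** One test at 0.05 leaves the error at 5% and, on this ground, 51 (57) per group unchanged.

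**The case against.** The best reply is that the intent can be inferred. Peroneal MNCV is the only variable used for the sample size and comes first in the list, the time point is fixed, and a condensed article leaves multiplicity procedures to an analysis plan that is not shown. Part of this stands: the absence of a named adjustment method is not in itself a fault here, and peroneal MNCV is probably what was meant. But an inference from the sample size paragraph does not prevent a sural or tibial result from being reported as the primary finding. Nor was space the obstacle: the Secondary outcome section names MNSI at week 4 as the most important secondary measure, while the three primary velocities are left unranked.

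A second objection concerns the size. The two-sided figures count errors in either direction, whereas the harm at stake is a false claim for LM. That is correct, so both are shown. The inflation relative to one test is similar.

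A reader might also infer a stronger case: three nerves on two legs make six primary tests, with an error of up to 1 − 0.95⁶ = 26.5%, or the legs might be analysed as if they were separate patients. The article supports neither. Measuring both legs describes data collection. The Sample size and Randomization sections count patients throughout, and nothing says that left and right are tested separately or used as units. How two legs become one value per patient is a detail that an article commonly leaves to the analysis plan.

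**Conclusion.** The point holds for the three nerves. The primary outcome section, the Abstract and the Discussion leave the deciding variable open, the Statistical analysis section sets no order, and the stated alpha and power fit only peroneal MNCV. If any one significant nerve counts as success, the two-sided error is roughly 8% to 14% instead of 5%, and the error favouring LM roughly 4% to 7% instead of 2.5%. The ranges rest on assumed correlations of 0 to 0.9 and on the any-nerve reading, which the article allows but does not state. Six-test or leg-as-unit figures should not be attached to this point.

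**What to change.** In the primary outcome section, state that the single primary endpoint is peroneal MNCV at week 4, the variable behind the sample size, with one pre-specified value per patient. The mean of the two legs is one acceptable choice; another single summary would also do if fixed in advance. List tibial MNCV and sural SNCV as secondary, and use the same definition in the Abstract, the Discussion, the Statistical analysis section and the registry entry. Do this before any NCV result is seen by group.

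If all three must remain primary, pre-specify Holm's procedure and restate the power, since 80% at 51 per group would no longer hold for a single nerve (about 66% at Holm's first step under the implied effect size).

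The first option costs a paragraph and a registry update, needs no new data and leaves 51 (57) per group unchanged on this ground. Its real price is that a sural or tibial result could no longer carry the primary claim. The second keeps all three nerves in play at the price of lower power or more patients.
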